## Discussion

### Implementation of the model

The development, evaluation, and dissemination of the Walcheren Integrated Care Model depends on its successful implementation. Research has shown that the implementation of integrated care is a very difficult and laborious task [66,67], especially regarding the proposed model because it focuses on integration across the entire continuum of care for all frail elderly. Other developmental strategies mainly focus on small programs for a targeted group or on a small part of the care process [26]. Additionally, when integrated arrangements are being implemented successfully in one setting, one is often unable to achieve dissemination on a wider scale [32]. Furthermore, developing integrated care arrangements is as much a process of social and cultural integration as it is structural integration. The success of implementation is shaped by the interests and cultures of the health professionals and the social relationships between them. Integration involves aligning the work of health professionals and convincing them to work together from a patient-centered viewpoint [29,68]. Several activities are and will be deployed to ensure that these challenges are overcome.

The involved professionals are all represented in a steering group that forms the umbrella under which the model is developed and disseminated. The steering group forms a Joint Governing Board that provides the necessary provider network, which is further strengthened with guidelines and protocol-led agreements. All patient representatives support the project, and the health insurer CZ is supporting the project financially. The basis for collaboration is also laid down in the formalization of agreements on the regional policy and involves integrated care for all elderly: the so-called ‘structured care of the elderly module.’ The project follows from these structures and will be able to make use of them.

Though administratively secure, the project will eventually be affected by the willingness of the partners to review tasks and delegate and accept new responsibilities thrust upon them. Acceptance of the role of a GP as coordinator is an essential aspect of this. GPs cannot claim this coordinating role for themselves. It will have to be given to them based on the confidence of all ‘players’ and by an agreement that a coordinating role for the GP is a suitable mechanism for improving the care for the frail elderly. A basis for this has already been established. The Walcheren GP Co-operation Care Group, the GP Co-operation in Veere, a working group of elderly patients and various partners in the region have agreed, within the recommendations and preconditions of the National Association for GPs (NHG), that creating a single entry point from the GP practices is the point of departure for setting up structured care of the elderly in Walcheren.

The feasibility of the experiment will also be enhanced by knowledge obtained in the region regarding instruments and collaboration that includes the elderly. Knowledge about using the GFI instrument was obtained during a pilot with the GFI instrument among elderly persons aged 85+ years. Consultations with elderly patients aged 65+ years have already started in three practices. Due to the broad involvement and experiences of health professionals, no major obstacles are expected regarding the model implementation. The pressures on providing care may increase for GPs because the use of the GFI instrument will provide them with information about the frail elderly who were previously unknown. This additional work pressure will be calculated in advance to prepare the GPs for the workload. The extra burden on GPs in the control region is particularly related to time registration and participation in interviews. These extra efforts will also be discussed with them in advance.

Embedding the experiment in other projects is essential over the long term. The experiment does not stand alone. A dementia care-chain and CVA care-chain are also being developed in Walcheren. The protocols developed will guarantee the link with the EASYcare instrument as used in this experiment. The steering group will ensure coherence between the various projects. The GPs in this project are also involved with developing the dementia care-chain. Their personal involvement in both projects will guarantee harmonization.

### Evaluation study

The choice for a quasi-experimental design instead of a randomized control trial may seem suboptimal to some. However, in many studies on organizational change, randomization is impractical, impossible or even undesirable [69]. This is the case in our study as health professionals cannot give traditional care and care according to the model at the same time. Blinding is impossible. For the elderly, it is undesirable to receive care from a different GP or organization from one previously used.

However, choosing for a quasi-experimental design presents our study with some challenges. The absence of randomization makes results subject to contamination by confounding variables [70]. Potentially confounding variables have been accurately defined based on literature, experiences of health professionals and comparable studies. Inclusion and exclusion criteria are set. However, there is no guarantee that some confounding variables will be missed. It is also conceivable that differences found in the experimental group are not the result of the intervention but of the additional attention given by both health professionals and interviewers [71]. It is debatable if this “Hawthorne-effect” is really problematic because increased and patient-centered attention for the frail elderly is one of the goals of the model. Irrespective of the design chosen, the biggest potential obstacle is the willingness of the elderly and their caregivers to participate in this study over the longer term. To increase willingness, a request to participate will be sent, as described above, via the elders’ own GPs, interviewers will be from the region and gifts will be given.

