**Quality of life**				
ICECAP	Interview elderly	x	x	x
EQ-6d	Interview elderly	x	x	x
SF-36	Interview elderly	x	x	x
Cantril’s self-anchoring ladder	Interview elderly	x	x	x
*Secondary outcomes*				

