### Study sample: sampling and eligibility criteria

Sampling will take place at GP practices in Walcheren. The experimental group will consist of the elderly patients of 8 GPs from 3 GP practices located in the east of Walcheren who will provide care according to the WICM. The control group will consist of 6 GPs from 5 GP practices in the north, south, and west of Walcheren who will provide traditional care. All elderly aged 75+ years in these practices who live independently will be asked to complete the GFI, along with several demographic questions and a consent form. Approximately 900 elderly in both the experimental and control practices will be contacted. The questionnaire is accompanied by a letter from the GP to raise the likelihood of response and assure that the elderly are well informed. After being sent a reminder, the elderly will be contacted by telephone or visited at home to be asked to participate and to help complete the questionnaire if necessary. These activities are expected to result in an 80% response rate. Elderly will be included if they score ≥4 on the GFI, if they have signed the consent form, or if they are able to make that decision themselves. Exclusion criteria are as follows: elderly on a waiting list for a nursing home, elderly who are not able to decide themselves if they want to participate (e.g., in case of dementia), and elderly with a life expectancy of <6 months due to a terminal illness. Included elderly will be asked to provide contact information for their informal caregiver. The caregivers will be contacted either by telephone or face-to-face during the first visit from the researchers at the home of the elderly subjects. They will be asked to fill in a written consent form if they agree to participate. Non-respondents will be contacted again by telephone. A response rate of 60% is expected. Health professionals will be selected based on their function and region of employment. An estimated 400 questionnaires will be sent to health professionals in the experimental and control groups. We expect a response rate of 50%.

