### Data collection and instruments: frail elderly

Outcome data and data on demographics (age, sex, living arrangement, education, and marital status) will be collected with questionnaires and file research at three points in time: T0, T1 (3 months after inclusion), and T2 (12 months after inclusion). Research has shown that effects can be expected 3 months after starting to use the EASYcare instrument [41]. The T2 measurement takes place to determine long-term effects. All elderly will be visited at home by trained interviewers recruited from the region of Walcheren to ensure a cultural fit with the elder. Interviewers will have a background in healthcare to ensure a high-quality interview. Every elder will be given a gift at T1 as a token of appreciation and to motivate further participation. File research will occur at the GP practices. The following instruments will be used (see Table 1):

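### The Discussion rules out all blinding, but its reasoning covers only care delivery and does not show that the interviewers who collect every primary outcome cannot be masked

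*Protocol article*

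**What the plan says.** The Discussion (Evaluation study) defends the quasi-experimental design. Randomisation is said to be unsuitable because "health professionals cannot give traditional care and care according to the model at the same time". The next sentence reads "Blinding is impossible", with no reason of its own and no distinction between professionals, participants and outcome assessors.

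Table 1 lists four primary quality-of-life instruments: ICECAP, EQ-6d, SF-36 questions and Cantril's ladder. For each the method is "Interview elderly", at T0, T1 and T2. The section on data collection for the frail elderly says that they are "visited at home by trained interviewers recruited from the region of Walcheren". It adds: "Interviewers will have a background in healthcare to ensure a high-quality interview".

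The arms are defined by place (Study sample). The experimental group comes from "3 GP practices located in the east of Walcheren", and the control group from five practices in the north, south and west.

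Interviewers appear once more in the Discussion, where a difference might be due to "the additional attention given by both health professionals and interviewers". The article then calls it debatable whether this matters, since patient-centred attention is a goal of the model.

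**The concern.** Care providers and participants plainly know which care is given and received. Interviewers are a third group, and nothing said about care delivery settles whether they must know the arm. The article takes a position on blinding that gives up assessor masking without a reason that reaches assessors.

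This matters because every primary outcome is subjective and passes through an interviewer, who can influence answers through tone, prompting and help with the questions. The EQ-6d also feeds the cost-utility analysis, so any distortion would carry into cost per QALY. In a non-randomised study, assessor masking is one of the few protections still available.

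The Hawthorne paragraph does not cover the point. Its defence is that extra attention belongs to the model. That can apply to professionals, but interviewing is not among the ten elements of the model. Both arms also have the same interview schedule, so interviewers can create a difference between arms only by acting differently by arm, which is the risk that masking addresses.

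**Working it through.** **1. Does the stated reason reach the interviewers?**

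| Group | Reason in the article why it cannot be masked |
|---|---|
| Health professionals | They cannot deliver both kinds of care at once (offered against randomisation) |
| Elderly participants | None stated for blinding, but they receive the care and know it |
| Interviewers | None |

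The blanket sentence therefore goes further than the text around it.

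**2. Does the planned adjustment deal with it?** The Data analysis section regresses the T2 score on the T0 score, research group and demographic variables. Let δ be the true effect, *s*₀ and *s*₂ the interviewer-related differences between arms at T0 and T2, and *b* the slope on T0. If the arms are otherwise alike and the shifts are additive, the group coefficient estimates

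δ + *s*₂ − *b*·*s*₀.

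- Stable difference in scoring (*s*₀ = *s*₂ = *s*): the bias is (1 − *b*)·*s*, so adjustment removes part of it.
- Expectation arising after the intervention starts (*s*₀ = 0): the bias is *s*₂, and adjustment removes none of it.

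**3. Scale.** The article gives no size for any interviewer effect, so this is a sensitivity calculation on assumed shifts.

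First, the number per arm behind the stated power. With the two losses added, 220 × (1 − 0.10 − 0.20) = 154. The noncentral t for two means has noncentrality *d*·√(154/2) = 8.775·*d*. At one-sided 5% this gives 0.9969 for *d* = 0.5 and 0.8369 for *d* = 0.3, matching the article's 0.997 and 0.837. Two-sided, the values are 0.992 and 0.747. The sidedness of the power calculation is a separate matter; here it only fixes 154 per arm.

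Now set the true effect to zero and let a shift of *B* SD between arms exist at T2. The two-sided false-positive rate (normal approximation, unadjusted comparison, independent observations) is

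1 − Φ(1.96 − 8.775·*B*) + Φ(−1.96 − 8.775·*B*).

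For *B* = 0.10: 8.775 × 0.10 = 0.8775, so 1 − Φ(1.0825) + Φ(−2.8375) = 0.1395 + 0.0023 = 0.142. The one-sided rate, for a shift favouring the model, is 1 − Φ(1.645 − 8.775·*B*).

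| Assumed shift *B* (SD) | Two-sided 5% test | One-sided 5% test |
|---|---|---|
| 0.05 | 7.2% | 11.4% |
| 0.10 | 14.2% | 22.1% |
| 0.15 | 26.0% | 37.1% |
| 0.20 | 41.9% | 54.4% |

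With sequential losses (220 × 0.9 × 0.8, about 158 per arm) the two-sided values are 7.3%, 14.4%, 26.6% and 42.8%. A shift in the other direction would hide a true effect instead.

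**The case against.** **This is a condensed article.** Interviewer assignment, visit lists and question order are fieldwork details that an article may leave to the full protocol. That is right, and their absence alone would be no finding. What stands is the explicit sentence: the article does not stay silent on blinding but declares it impossible.

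**The sentence may mean only professionals and participants.** The link to the preceding reason rests on adjacency, and the paragraph is about care delivery. This reading is fair. On it, narrowing the sentence costs nothing, and the status of the interviewers remains to be stated.

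**Masking would be partial.** This stands. Arms are geographic and interviews take place at home, so the address may suggest the arm. Care use and experience of care are asked at all three time points, so asking them last does not protect a later visit by the same interviewer. The elderly are unblinded self-reporters, and masked interviewers would leave that reporting bias untouched. A promise that interviewers will be blinded would therefore claim too much.

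**Stronger readings that the article does not support.**

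- A reader might infer that interviewers work in one area only and are confounded with arm. The article recruits them from Walcheren, which contains both arms, and says nothing about assignment.
- A reader might infer that interviewers are employed by partner organisations and should be barred. Nothing says so, and a blanket exclusion would sit badly with the call for local interviewers with a healthcare background, because the professionals involved are all represented in the steering group.
- A reader might infer that a third to two thirds of the planned effect could come from the assessors. That takes an assumed shift of 0.1 to 0.2 SD and divides it by 0.3. The Power calculation section assumes 0.5 first, against which the same shift is 0.1/0.5 = 20% to 0.2/0.5 = 40%. The shift itself has no source in the article.

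**Conclusion.** The point holds in a limited form. The Discussion rules out all blinding, while the reason beside it concerns care delivery only and does not show that the interviewers collecting all four subjective primary outcomes cannot be masked. Unmasked interviewers could bias the quality-of-life comparison. The article does not support saying that they do.

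Size and direction are unknown. The false-positive rates above rest on an assumed shift, on 154 per arm, and on an unadjusted comparison of independent observations; they show only that a small shift would matter. Adjustment for the T0 score would remove part of a stable difference in scoring, but not expectation that arises after the intervention starts. This is a cheap improvement in wording and fieldwork, and does not show that the design fails.

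**What to change.** 1. Limit the sentence to the groups it fits: professionals and participants cannot be blinded; interviewers will be masked to research group as far as feasible.
2. State three measures. Visit lists carry neither practice nor arm. Each interviewer visits elderly from both experimental and control practices in similar proportion. The four primary instruments are asked before the care-use, CQ-index and coordination questions.
3. Name the residual assessor and self-report bias as a limitation, because arms are geographic, visits are repeated and participants know their care.

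The second measure helps even where masking fails, because it keeps interviewer-specific scoring from lining up with arm. Question order costs nothing at the first visit and protects less at later ones.

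The cost is a change of wording, some extra scheduling and some extra travel within Walcheren. The gain is a reduction of possible assessor bias, not its removal.

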## Abbreviations

WICM: Walcheren Integrated Care Model; GP: General practitioner; GFI: Groningen Frailty Indicator; SF-36: Short form (36) health survey; ICECAP: Index of capability for older people; EQ-6d: EuroQol (6 dimensions); SRB: Self-related burden; VAS: Visual analogue scale; CSI: Caregiver strain index; ASIS: Assessment of the Informal Care Situation; CSAI: Community Service Attitude Inventory; iBMG: Institute of Health Policy and Management; Qaly: Quality adjusted life years; Dalys: Disability adjusted life years; CQ-index: Consumer quality index.
